## 8.3. Multivariate analysis

*Primary outcome measures*

Using multiple regression, a predicted model can be formulated, in which performance on the Dot Counting Task can be predicted from several variables, such as group allocation (training group vs. control group).

*Secondary outcome measures*

The effect of training on the questionnaires, scanning tests, mobility tests and the reading test will be examined using multivariate analysis (MANOVA or mixed design ANOVA), so we can control for familywise error rate.

In addition, the effect of training will be examined by comparing test performance in the control group with the preceding measurement using multivariate analysis (MANOVA for multiple repeated measures design: 1 group, 3 time points, several outcome parameters).

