# 2. OBJECTIVES AND RESEARCH QUESTIONS

Primary:

The aim of this study is to examine the effect of a compensatory scanning training (CST). The effects will be investigated on the level of functions, activities and participation.

The expectation related to the training is that patients learn to make larger and more efficient saccades towards the blind hemifield, shifting potentially interesting objects into the functional healthy part of the visual field, enlarging the visual field of search and decreasing search time. Herewith we strive to improve general mobility, increasing participation and quality of life.

The following research questions have been defined:

*1. Does CST result in larger, more frequent and faster saccades to the blind hemifield?*

*2. Does CST result in more accurate and faster detection of peripheral visual stimuli?*

*3. Does CST result in shorter search times in complex visual environments?*

*4. Does CST result in safer participation in slow traffic?*

*5. Does CST result in less bumping to objects in complex visual environments?*

*6. Does CST result in a decrease in self-reported visual disabilities?*

*7. Does CST result in increased self-reported mobility?*

*8. Does CST result in improved self-reported quality of life?*

The order of presentation reflects the build-up of possible causal relations regarding the possible effect of the intervention.

Secondary:

Furthermore, the predicting effects of several variables will be examined.

The following aspects will be examined:

1. Visual functions, of which size of the visual field defect is the most important
2. Awareness and understanding the HVFD and its consequences in daily life.
3. Motivation for training
4. Presence of important health changes and life events during and preceding the study.
5. Premorbid level of intelligence
6. Executive functioning
7. Memory

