## 4.4. Sample size

The sample size was based on previous studies on the effect of CST. There is no reason to expect negative effects of training. Therefore, calculation of sample size was based on one-sided testing. Section *6.1.1 Primary outcome measures* provides more information on the reasons for eye movement parameters as primary outcome parameters. The Effect Size (ES) is calculated based on previous studies on the effect of CST on the number of fixations and refixations [2,5]. Taking the lowest value encountered (ES = 0.65), a minimum of 30 participants per group is required (training group vs. control group; two independent groups; α = 0.05; β = 0.20; one-sided testing). When comparing pre and post assessments within the total group (n=60), an ES of 0.34 can be detected with power 0.80 and one-sided testing with 0.05 significance. This means that even in case of low effectiveness of compensatory scanning training, the group size is fully sufficient. We assume an inflow of 120 patients (n=120) and we take into account a loss of 30 patients (25%) based on medical history (remaining n=90), 15 patients (17%) after assessment of inclusion and exclusion criteria (remaining n=75), and 15 patients (20%) during the period of training and effect measurements (remaining n=60).

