### 6.1.2. Secondary outcome measures

*Visual functions:*

- Visual field, with Goldmann (2x monocular)
- Visual acuity, with ETDRS 2000 letter chart at 500 lux
- Contrast sensitivity, with Gecko at 500 lux

*Questionnaires (see also F1.Questionnaires)*:

- Awareness; based on theories on awareness by Crosson [7] and Critchley [8] and piloted in a group of patients with hemianopia.
- Life events; questions based on the Life Events Questionnaire (LEQ) [9].
- Motivation; questions selected from Motivation for Traumatic Brain Injury Rehabilitation Questionnaire (MOT-Q) [6].
- Expectations/Evaluation of training; questions based on interviews from previous master thesis research at UMCG Beatrixoord.
- NEI-VFQ25 (National Eye Institute - Visual Functioning Questionnaire/25 items, Dutch translation)
- VOM (Vragenlijst Onafhankelijke Mobiliteit, Dutch translation of the Independent Mobility Questionnaire)
- CVD (Cerebrale Visuele Stoornissen, Dutch translation by M. L. M. Tant, 1997)

*Neuropsychological testing:*

- Grey Scales
- NLV (Nederlandse Leestest voor Volwassenen)
- Zoo-map (BADS)
- 15-Words Test

*(Ecological) scanning and mobility tests:*

- Dot Counting Task (with eye tracking); dots are presented on a large screen and are to be counted by the patients.
- Standardized search task (with eye tracking); search task on a large screen; patients have to indicate whether or not a target is present among distractors.
- Hazard perception pictures (with eye tracking); photos of traffic situations; patients have to indicate what action they would perform in the given situations: brake, release gas pedal or do nothing.
- Hazard perception movie clips (with eye tracking); short movies of traffic situations; patients have to indicate which overt and covert hazards are present.
- Tracking Task; test in which the patient tries to keep an imaginary car on the road in the presence of cross wind using a steering wheel (road is depicted on a central monitor) while simultaneously reacting on stimuli in the left and right periphery.
- Rides in a driving simulator
- Mobility test; walking through a corridor, with and without obstacles and with and without a cognitive dual task (digit span).

*Test for cross validation:*

- Reading test

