# 8. STATISTICAL ANALYSIS

Alpha=0.05 will be applied for all statistical testing.

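### The stated familywise error control for the secondary outcomes does not hold for conclusions on individual outcomes

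*Protocol*

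**What the plan says.** Section 8.3 of the protocol groups the secondary outcomes as questionnaires, scanning tests, mobility tests and the reading test. It says the effect of training on them "will be examined using multivariate analysis (MANOVA or mixed design ANOVA), so we can control for familywise error rate". The two methods are offered as alternatives. Section 8 adds: "Alpha=0.05 will be applied for all statistical testing". No adjusted level and no other multiplicity safeguard appears in the document.

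Section 2 poses eight separate research questions. Question 1 concerns eye movements, the primary outcome. Questions 2 to 8 concern detection, search time, safety in slow traffic, bumping into objects, self-reported visual disability, self-reported mobility and quality of life. Of their sequence the protocol says: "The order of presentation reflects the build-up of possible causal relations regarding the possible effect of the intervention".

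Section 4.4 sizes the trial on a single univariate comparison with an effect size of 0.65 and 30 patients per group, and "calculation of sample size was based on one-sided testing".

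**The concern.** Questions 2 to 8 ask about seven different constructs, so answering them takes a conclusion on each. A global rejection says only that something differs somewhere. The protocol presents the method as sufficient for error control, and a reader of the results would take a significant finding on mobility or quality of life to be covered by that control. Section 6.1.1 itself rates these outcomes as clinically more important than the eye movement parameters. If the control is not real, the most consequential secondary claims carry a higher false-positive risk than the protocol tells its readers.

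**Working it through.** **Inputs from the protocol.** 60 patients (section 4.1), 30 per group, effect size 0.65, one-sided 0.05 and power 0.80 (section 4.4); 0.05 for all tests (section 8). The number of secondary variables is not given. Counting instruments in section 6.1.2 gives 7 scanning and mobility tests, 1 reading test and 3 to 7 questionnaires, so 11 to 15. The Dot Counting Task is in that list although it is also the primary task, and an instrument can yield several variables, so 8 to 15 is used as a working range.

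**Assumptions.** Equal correlation of 0.3 between outcomes (0 and 0.5 as sensitivity), two-sided follow-up t-tests at 0.05 without baseline adjustment, and one MANOVA over all outcomes. The protocol states none of these.

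**Step 1: the plan's own figure.** n per group = 2(1.645 + 0.842)² / 0.65² = 29.3, rounded up to 30. Exact one-sided t power at 30 per group is 0.800. The figure reproduces. It covers one univariate comparison and does not bear on error control across secondary outcomes.

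**Step 2: separate tests, no outcome affected.** For k independent tests the chance of at least one false positive is 1 − 0.95^k: 0.34 for k = 8, 0.43 for k = 11 and 0.54 for k = 15. At correlation 0.3, simulation gives about 0.30 to 0.31, 0.38 and 0.46. This is the situation if a mixed design ANOVA is run for each outcome.

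**Step 3: MANOVA first, then single outcomes.** With two groups the MANOVA is Hotelling's T² on p and 60 − p − 1 degrees of freedom. Each run tests it at 0.05 and, if it is significant, tests each outcome at 0.05. Simulated results at correlation 0.3 (20,000 trials per row for 8 outcomes, 8,000 for the others):

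| Truly affected | Outcomes | MANOVA significant | At least one false claim, after MANOVA | At least one false claim, separate tests |
|---|---|---|---|---|
| none | 8 | 0.05 | 0.04 | 0.30 |
| none | 11 | 0.05 | 0.05 | 0.38 |
| none | 15 | 0.05 | 0.04 | 0.46 |
| one at 0.65 SD | 8 | 0.42 | 0.17 | 0.27 |
| one at 0.65 SD | 11 | 0.35 | 0.18 | 0.35 |
| one at 0.65 SD | 15 | 0.29 | 0.19 | 0.44 |
| three at 0.65 SD | 11 | 0.81 | 0.27 | 0.30 |
| three at 0.65 SD | 15 | 0.77 | 0.34 | 0.39 |

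False claims are counted among unaffected outcomes only. The MANOVA holds 5% in the first three rows, where nothing responds. Once some outcomes respond, the gate opens and the remaining tests run unprotected. Across correlations 0 to 0.5 with 11 or 15 outcomes, the after-MANOVA rate is 0.17 to 0.20 with one affected and 0.24 to 0.36 with three affected at 0.65 SD.

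**Step 4: power of the global test.** The noncentrality is λ = 15 · δ′R⁻¹δ, where δ holds the standardised effects and R the correlations. With 11 outcomes and correlation 0.3:

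- One affected: λ = 15 × 0.4225 × 3.7/2.8 = 8.37, power 0.36.
- Three affected: λ = 15 × (0.4225/0.7) × (3 − 0.675) = 21.05, power 0.82.
- For comparison, a single two-sided t-test at 0.65 SD has power 0.70.

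So the omnibus test can lose power when one or few outcomes respond, but not when several do.

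**Step 5: the alternative.** In runs of the same kind, Holm held the chance of any false claim at 3 to 5%.

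**The case against.** The strongest defence is that section 8.3 specifies no follow-up tests. A global test followed by an adjusted procedure is legitimate, and the details may sit in an unseen SAP. That is fair as far as it goes: the absence of a follow-up procedure is not the fault here, and the unadjusted 5% follow-ups in the working are an assumption resting on section 8's general alpha. What remains is that the protocol credits the method itself with a property it lacks for single outcomes. Separate MANOVAs per domain would also fit section 8.3, but they would need adjustment across domains.

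A reader might infer more than the document supports:

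- **That MANOVA is underpowered here in general.** Step 4 shows this depends on the effect pattern, and the causal chain in section 2 suggests that several levels may respond. Holm does not recover the loss either: over seven outcomes with one affected, its power for that outcome is about 0.41, against 0.45 for the omnibus test.
- **That predictors are tested as outcomes.** The clarification in section 6.1.2 names NEI-VFQ25, VOM and CVS, plus the evaluation questionnaire, as the activity and participation measures. Section 2 lists awareness, motivation and life events as predictors. Section 8.3 is only loosely worded. Premorbid intelligence is assessed under neuropsychological testing, which section 8.3 does not include.
- **That patients with any missing variable are dropped.** This is a common software default; the protocol does not state it.

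**Conclusion.** The error-control statement in section 8.3 is wrong as written for conclusions on individual secondary outcomes. It is true only of the global hypothesis that nothing differs, which is not the situation a trial expecting training to work is planning for. Under the stated assumptions, the chance of at least one false claim is about 17 to 19% with one of 8 to 15 outcomes affected at 0.65 SD and about 27% with three of 11. It is about 30% or more for separate tests of 8 or more outcomes with none affected. These sizes depend on the assumed outcome count, correlation and follow-up rule; the direction does not. The point concerns secondary outcomes and leaves the primary comparison and its sample size untouched. It should be corrected, and an unseen SAP would not make the protocol's sentence true.

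**What to change.** 1. Delete the claim that MANOVA or mixed design ANOVA controls the familywise error rate.
2. Name one variable for each of research questions 2 to 8. Test each between groups at T2, adjusted for its T1 value.
3. Apply a procedure with strong control over those seven tests: Holm, or a fixed sequence in the stated order of the questions. A global MANOVA may still be reported alongside. In a fixed sequence, testing stops at the first non-significant result, so the self-reported outcomes at the end could be claimed only if all earlier questions succeed.
4. Label all other secondary variables exploratory.
5. State that the questionnaires in section 8.3 are the outcome questionnaires named in the clarification in section 6.1.2, and that awareness, motivation and life events remain predictors.

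The cost is wording, with no extra patients or measurements. Seven variables must be fixed before unblinding, and the remaining variables lose confirmatory status.

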5. In case the patient is included and has given informed consent, the patient is randomly allocated to the training group or control group (method of minimization, see for more information section *6.2 Selection*). Allocation to one of the two groups will not affect the moment at which the training starts. At Royal Dutch Visio, a waiting list of several months preceding treatment is not unusual. Patients from both the training group and the control group will visit the University Medical Center Groningen for a pre-assessment (the week before onset of training at Royal Dutch Visio) and a post-assessment (after 10 weeks of training). The control group will participate in a third assessment, 10 weeks before the pre-assessment (the so-called -10 assessment). By looking at the results from the pre-assessment and post-assessments of the training group and the results from the -10 assessment and pre-assessment of the control group, the effect of 10 weeks of training is compared to the effect of 10 weeks on the waiting list. In addition, the effect of treatment on the individual level can be examined by comparing the results from the post-assessment to the results from the -10 assessment and pre-assessment in the control group (within-patient repeated measures design). Including the post-assessment in the control group also increases power of the study.

In order to provide compensatory scanning training close to the patients’ residence, training will be provided at several locations of Royal Dutch Visio throughout the Netherlands, including Haren, Leeuwarden, Apeldoorn, Rotterdam and Haarlem. The final training protocol is composed in Haren. Therapists working at the participating departments of Visio received additional education in providing the training conform protocol. The training and diagnostic assessments take place at the department of Visio where the patient has registered.

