## 8.2. Univariate analysis

*Primaire onderzoeksparameter*

The effect of training on the fixation and saccade parameters on the Dot Counting Task are analyzed in two ways:

1. A between-group analysis by comparing data from T2 of the training group with data from T2 of the control group, possibly corrected for data from T1.
2. A within-group analysis by comparing change between T1 and T2 with change between T2 and T3 in the control group using repeated measures analysis.

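### The added within-control-group MANOVA in Section 8.3 cannot separate a training effect from retest change on the secondary outcomes

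*Protocol*

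**What the plan says.** Protocol Section 8.3 first plans a MANOVA or mixed design ANOVA for the effect of training on the questionnaires, scanning tests, mobility tests and reading test. It then adds that "the effect of training will be examined by comparing test performance in the control group with the preceding measurement using multivariate analysis", and describes the model as "MANOVA for multiple repeated measures design: 1 group, 3 time points, several outcome parameters".

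Section 3 fixes where the three control-group time points lie. All patients are assessed in the week before training starts (pre) and after 10 weeks of training (post). In addition, "The control group will participate in a third assessment, 10 weeks before the pre-assessment" (the -10 assessment). So -10 to pre is waiting without training, and training falls only between pre and post. The main comparison in Section 3 is the randomised one, in which "the effect of 10 weeks of training is compared to the effect of 10 weeks on the waiting list".

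For the primary outcome, Section 8.2 words the within-control analysis differently: "A within-group analysis by comparing change between T1 and T2 with change between T2 and T3 in the control group using repeated measures analysis". Section 8.3 states no such contrast for the secondary outcomes. Section 3 describes the within-patient comparison in yet another way, as post set against both -10 and pre.

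**The concern.** The analysis is offered as a way to examine the effect of training, but the named test addresses a different question. A repeated-measures MANOVA in one group with three time points has as its overall null that the outcome means are equal at -10, pre and post. Patients repeat the same search, hazard, tracking, simulator, mobility and reading tasks at each visit, so familiarity alone could move the means. If only post against pre is tested, the change seen during waiting is still not subtracted.

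At stake is how a significant result is read. The secondary outcomes bear on research questions 2 to 8, and Section 6.1.1 regards the mobility and quality-of-life questionnaires as clinically more important than the eye movement parameters. A result from this analysis could be taken as evidence for training when it shows only change over time. Excluding that explanation is the purpose of the waiting-list control.

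**Working it through.** **The plan's own figure.** Section 4.4 gives 30 per group for an effect size of 0.65, one-sided alpha 0.05 and power 0.80. This reproduces: two-sample t-test power at 30 per group is 0.800. The protocol gives no error rate for the one-group MANOVA, so the rest is new calculation.

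**Inputs from the protocol.** n = 30 controls (Section 4.4); alpha 0.05 (Section 8); time points -10, pre, post (Section 3).

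**Assumptions, not in the protocol.** p = 3 outcomes with SD 1; correlation between visits r = 0.7; correlation between outcomes 0.3; the same retest gain d on every outcome; training effect zero.

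**Method.** Exact power of the one-sample Hotelling T² test on the relevant time contrasts, from the noncentral F distribution with q and n - q degrees of freedom (q = number of contrasts × p). Let k = p / [1 + (p - 1) × 0.3] = 3 / 1.6 = 1.875, so n × k = 56.25. The noncentrality is L.

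*Post minus pre* (q = 3). Variance of the difference is 2(1 - r) = 0.6.
- Steady gain d per visit: L = 56.25 × d² / 0.6. For d = 0.2, L = 3.75; for d = 0.3, L = 8.44.
- Gain only between -10 and pre: L = 0.

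*Overall time effect* (q = 6), on the two successive differences.
- Steady gain: L = 56.25 × 2d² / 0.3. For d = 0.2, L = 15.0; for d = 0.3, L = 33.75.
- Gain only between -10 and pre: L = 56.25 × (2/3)d² / 0.3. For d = 0.2, L = 5.0; for d = 0.3, L = 11.25.

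*Difference of changes*, (post - pre) - (pre - [-10]) (q = 3). Variance is 6(1 - r) = 1.8.
- Steady gain: the mean is zero, so L = 0.
- Gain only between -10 and pre: the mean is -d, so L = 56.25 × d² / 1.8. For d = 0.2, L = 1.25; for d = 0.3, L = 2.81.

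**Rejection rates with no training effect** (each pair is d = 0.2 / d = 0.3):

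| Test | Steady gain per visit | Gain only before training |
|---|---|---|
| Overall time effect | 72% / 98% | 26.5% / 58% |
| Post minus pre | 30% / 61% | 5% / 5% |
| Difference of changes | 5% / 5% | 12% / 23%, against training |

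With no change at all, every test holds 5%. Simulation of the d = 0.3 setting (20,000 runs) agrees: under steady gain 98%, 60% and 5%; under gain before training only 58%, 5% and 23%.

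**Range.** Over 1 to 8 outcomes, r from 0.5 to 0.7 and gains of 0.2 to 0.5 SD, steady gain gives 14% to 98% for post minus pre and 27% to 100% for the overall time effect.

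**Randomised comparison.** In simulation (4,000 runs per setting), comparing the training arm's pre-to-post change with the control arm's -10-to-pre change rejected in 4% to 6% of trials throughout. Both arms are then compared over their first two assessments, so an equal retest gain cancels.

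**The case against.** The strongest reply is that the wording points to successive contrasts, with the bracket merely describing the data layout. On that reading change confined to the waiting period does no harm, because post minus pre stays at 5%. This stands. A reader might infer that the planned test will signal a training effect even when all change came before training. The protocol does not support that as a general statement, since it applies only if the overall time effect is taken as the test of training. Steady retest change still inflates post minus pre.

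Second, the analysis is an addition. The preceding sentence plans a MANOVA or mixed ANOVA, which can carry the group-by-time term, and Section 3 makes the randomised comparison the main one. This also stands. It would be going too far to say that the secondary conclusions rest on the one-group test or that it displaces the control group.

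Third, successive comparisons would display the waiting change beside the trained change. True, but no formal comparison of the two is stated.

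Fourth, contrasts are often left to the SAP. Here, however, the protocol itself names a test and its purpose, and the two do not match, while Section 8.2 states a suitable contrast for the primary outcome.

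Fifth, the gains are assumed. Six months since onset and a stable neurological condition (Section 4.2) limit recovery, and practice gain on self-report questionnaires is not obvious. The percentages are therefore illustrative. The mismatch itself does not depend on them.

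**Conclusion.** The point holds in limited form. As worded, the one-group, three-time-point analysis does not separate training from retest change under either reading. For assumed steady gains of 0.2 to 0.3 SD per visit, 3 outcomes, correlation 0.7 between visits and 0.3 between outcomes, n = 30 and no training effect, post against pre rejects in about 30% to 61% of trials and the overall time effect in 72% to 98%. If retest change is absent there is no inflation. Vulnerability to change lying wholly before training belongs to the overall time effect alone.

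Severity is minor to moderate: the analysis is supplementary, concerns secondary outcomes, and sits beside an analysis that can use the randomisation.

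**What to change.** In Section 8.3, state that training-effect claims on the secondary outcomes rest on the randomised comparison: training arm pre to post against control arm -10 to pre, as the group-by-time term or as the group effect at T2 given T1.

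If the within-control analysis is kept, replace the overall time effect and the post-against-pre comparison with the directed contrast (post minus pre) minus (pre minus -10), in line with Section 8.2, and label it supportive only.

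The cost is wording and a different contrast on data already planned, with no extra patients or visits. The contrast has drawbacks:
- It is noisier than post minus pre: variance 1.8 against 0.6 in the example, so its standard error is √3 ≈ 1.7 times as large.
- It is valid only if retest change is equal in both intervals. If the gain fades, it understates a true effect: with 0.3 SD in the first interval and 0.15 SD in the second, by 0.15 SD.
- A multivariate test of it is non-directional, so the direction of the estimates must be checked before a rejection is read as benefit.

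For these reasons it should not carry a claim alone.
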